## Abstract

**Background:**

To our knowledge, to date, 52 patients with thumb carpometacarpal osteoarthritis (CMC1 OA) were treated with joint distraction. So far, most patients experienced improved physical function and less pain. After 2 years, only 1 patient proceeded to trapeziectomy. This study assesses if we can safely lower the distraction duration from 8 to 6 weeks for CMC1 joint distraction, maintaining the improvement in physical function and pain.

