**Discussion:**

If safe, the duration of basal thumb joint distraction can be reduced to 6 weeks, reducing patient burden. Because this is a relatively new treatment, this trial will provide greater knowledge of potential adverse events. This knowledge allows for more informed decision making for patients considering CMC1 distraction treatment. Future studies can directly compare joint distraction to other treatments of CMC1 joint arthritis like splinting and trapeziectomy.

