### Study objectives

The primary objective is to assess if 6 weeks of CMC1 joint distraction is not inferior to a duration of 8 weeks. Our primary outcome is physical function measured with the Patient-Reported Outcomes Measurement Information System Physical Function for the Upper Extremity (PROMIS UE) at 1 year after distraction.

Our secondary objectives are:
We hypothesize that there is no difference between groups in terms of pain intensity, patient satisfaction, joint stiffness, thumb function, range of motion, and strength at 1 year.We hypothesize that there is no difference in hand health status measured with the Michigan Hand Outcome Questionnaire (MHQ) between the 6-week and 8-week group at 1 year.We will investigate if there is a difference in adverse event rate and treatment failure at 1 year.We will measure minimal joint space width on radiographs at 1 year and test if there is a difference between the two groups.We will assess symptoms of depression and catastrophic thinking (captured by 2 short questionnaires) since there is mounting evidence that psychosocial factors influence symptom intensity and magnitude of physical limitations among patients with CMC1 OA [20–22]. We will test if these, and other factors, are independently associated with physical function and hand health status.To study the long-term effects of joint distraction in the treatment of CMC1 OA, we will test all hypotheses mentioned above at 2 years and 5 years post-distraction.

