### Statistical analysis

The following characteristics will be reported in the baseline characteristics table: age, gender, work status, marital status, level of education, PROMIS UE scores, MHQ, PHQ-2, PCS-4, VAS for pain, satisfaction, thumb stiffness, thumb function, range of motion, strength, and joint space width on radiographs. Testing for differences in baseline characteristics among groups will only be done if visual inspection of the results indicates possible significant differences.

The primary outcome will be the difference in PROMIS UE score between the 6-week group (A) and 8-week group (B) at 1 year follow-up. We will report the mean with SD and 95% CI and the mean difference with 95% confidence interval. If the mean difference with 95% CI falls within the predefined non-inferiority margin of 9.0 points of PROMIS UE scores, we will conclude non-inferiority.

Regarding the secondary hypotheses, we will test for superiority between the 6-week and 8-week group.
We will assess any differences in MHQ scores, VAS pain, VAS satisfaction, VAS function, VAS stiffness, range of motion, and strength at 1 year follow-up compared to baseline. We will test for superiority between groups by comparing the mean differences at 1 year.Treatment failure is scored when a patient proceeds with an invasive surgical procedure (f.e. trapeziectomy) after distraction therapy due to ongoing symptoms of CMC1 OA. We will analyse the difference between groups in the proportion of participants who are classed as treatment failure at 1 year.Adverse event rates will be reported and classified according to the Clavien-Dindo classification of surgical complications. We will analyse the difference between groups in the proportion of participants who are classed as adverse event at 1 year.Joint space width at 1 year follow-up is compared to baseline measures in both groups. Mean difference in mm between groups is assessed at 1 year follow-up.

This will be intention-to-treat analyses. In case of non-adherence, to test the robustness of our results, we will also report the results of per-protocol analyses [33].

We will create 2 multivariable linear regression models to assess factors independently associated with PROMIS UE and MHQ scores at 1 year. In these models, we will include all mentioned study parameters (except PROMIS UE and MHQ scores) with *P* < 0.10 in bivariate analysis. *P* values < 0.05 are considered statistically significant.

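### The plan hypothesises no difference in pain, hand health, motion and strength but tests these outcomes for superiority, which cannot support that hypothesis

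*Protocol article*

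**What the plan says.** All references are to the protocol article.

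- **Study objectives, first secondary bullet:** "We hypothesize that there is no difference between groups in terms of pain intensity, patient satisfaction, joint stiffness, thumb function", continuing with range of motion and strength, at 1 year. The second bullet makes the same hypothesis for MHQ.
- **Study objectives, other bullets:** adverse events and treatment failure are worded differently: "We will investigate if there is a difference in adverse event rate and treatment failure at 1 year". Joint space width is likewise to be tested for a difference.
- **Abstract, Background:** the aim is to shorten distraction while "maintaining the improvement in physical function and pain".
- **Statistical analysis:** "Regarding the secondary hypotheses, we will test for superiority between the 6-week and 8-week group". For MHQ, the VAS scores, range of motion and strength it adds: "We will test for superiority between groups by comparing the mean differences at 1 year". The same analyses are repeated at 2 and 5 years.
- **Sample size calculation and Statistical analysis:** a non-inferiority margin (9.0 points) and a power calculation are given for PROMIS UE only.

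**The concern.** For the patient-reported, motion and strength outcomes, the expected finding is sameness and the planned tool is a test for difference. The only test result that agrees with the stated hypothesis is a non-significant one. Such a result can come from true similarity or from too little information, and the test cannot tell these apart.

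The authors handle this correctly for PROMIS UE, where the CI is judged against a margin. They drop that logic for outcomes with the same not-worse purpose. Pain is the clearest case, because the abstract puts it next to physical function as a benefit to be maintained. At stake is what the trial may say about pain and hand health if 6 weeks is moderately worse.

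**Working it through.** **1. The plan's own figure.** Inputs from Sample size calculation: margin 9.0, SD 11, power 90%, one-sided 2.5%, loss 5%. Allocation is 1:1 (Randomization and blinding). A true difference of 0 is assumed.

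- n per arm = 2 × (1.960 + 1.282)² × (11/9)² = 31.4, rounded up to 32, so 64 in total.
- 64 / 0.95 = 67.4, rounded up to 68. The stated 68 is reproduced.

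**2. Precision for a continuous secondary outcome.** Assumptions: 32 evaluable patients per arm and a two-sided 5% test. Differences are in SD units because the article gives no SD for these outcomes.

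- Standard error = √(2/32) = 0.25 SD.
- 95% CI half-width = 1.96 × 0.25 = 0.49 SD (0.50 with the t distribution).
- Difference detectable with 80% power = (1.960 + 0.842) × 0.25 = 0.70 SD.

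**3. Power by true difference d**, as Φ(d/0.25 − 1.96):

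| True difference (SD) | Power | Chance of non-significance |
|---|---|---|
| 0.2 | 12% | 88% |
| 0.3 | 22% | 78% |
| 0.5 | 52% | 48% |
| 0.7 | 80% | 20% |
| 0.82 (the primary margin, 9/11) | 91% | 9% |

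With the t distribution, power at 0.5 SD is 50% and at 0.82 SD it is 90%.

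**4. What a non-significant result leaves open.** An observed difference of exactly zero still has a CI reaching a deficit of 0.49 SD. An observed deficit just short of significance has a CI reaching 0.49 + 0.49 = 0.98 SD. Suppose, for illustration only, that a secondary outcome had a margin of 0.82 SD. An observed deficit between 0.82 − 0.49 = 0.33 SD and 0.49 SD would then be non-significant and yet fail the kind of rule used for the primary outcome.

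**5. If a margin were used instead.** Non-inferiority at one-sided 2.5%, true difference 0, assumed margin m in SD units:

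- m = 0.5: power with 32 per arm = Φ(0.5/0.25 − 1.96) = 52%. For 80% power, 2 × (1.960 + 0.842)² / 0.5² = 62.8, so 63 per arm; for 90%, 85 per arm.
- m = 0.8: power with 32 per arm = Φ(0.8/0.25 − 1.96) = 89%. For 80% power 25 per arm are needed, for 90% 33.

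**The case against.** **No difference may only be the formal null hypothesis, loosely worded.** The abstract's Methods also describes the secondary outcomes as identifying differences, with pain and hand health among them. This reading is possible but less natural. The authors say that they hypothesise sameness, and in the same list they word adverse events, treatment failure and joint space as open questions. If the null was meant, rewording is still needed.

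**A reader might infer that the trial will report P > 0.05 as equivalence.** No sentence says so. The only rule for a positive conclusion is the CI-against-margin rule for PROMIS UE. The stated hypotheses invite the inference, and nothing in the article guards against it, but it remains an inference.

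**A reader might extend the point to complications,** since the abstract's Discussion says "If safe, the duration of basal thumb joint distraction can be reduced to 6 weeks". The documents do not support that. Adverse events and treatment failure are open questions, which a difference test fits, and the sentence does not say that safety would be judged from non-significance. Low power for pin tract infection would not hide harm from 6 weeks either, because the article expects fewer such infections in that group.

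**A reader might add a multiplicity charge.** Thirteen secondary outcomes at three time points give 1 − 0.95¹³ = 49% and 1 − 0.95³⁹ = 86% chance of at least one false positive, but only if the tests are independent. These are related measures, repeated in the same patients. With an assumed common correlation of 0.5 the figures fall to about 33% and 56%. Multiplicity among secondary outcomes is also commonly left to an analysis plan, and the article's P < 0.05 sentence closes its regression paragraph, so its reach over every secondary test is assumed.

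**Could the analysis plan settle it?** This is not an omission. The article states both the hypotheses and the test, and they do not match.

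**Conclusion.** The point holds for pain, satisfaction, stiffness, thumb function, range of motion, strength and MHQ, at 1 year and in the repeats at 2 and 5 years. The planned test cannot support the stated hypothesis. With 32 evaluable patients per arm, a true deficit of 0.5 SD would look consistent with no difference about half the time, and one of 0.3 SD about 78% of the time.

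These sizes rest on a two-sided 5% level and on effects assumed in SD units. They do not mean that any deficit would be missed: power is about 90% at 0.82 SD. Nor do the documents give a basis for requiring particular margins for VAS pain or MHQ.

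The primary outcome, its margin, the sample size of 68 and the primary conclusion are untouched. This should be fixed, because it decides what may be said about pain and hand health, but it is not a fault in the trial's main comparison.

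**What to change.** For the seven outcome groups named in the verdict:

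1. In Study objectives, reword the two no-difference bullets as estimating the difference between 6 and 8 weeks.
2. In Statistical analysis, replace the superiority test for these outcomes by the between-group mean difference with its 95% CI, at 1, 2 and 5 years.
3. Add one sentence: a non-significant result will not be taken as evidence of no difference or of maintained benefit.
4. If a maintained claim for pain or MHQ is wanted, prespecify a justified margin before outcome data by group are examined, and judge the CI against it. Otherwise drop the claim. Patients, surgeons and hand therapists are not blinded, so the margin should be dated and documented before any comparison by group.

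Difference tests can stay for adverse events, treatment failure and joint space.

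The cost is wording and, if chosen, the justification of one or two margins. No patients, visits or measurements are added. The downside is that some hoped-for no-difference statements become inconclusive. With a margin as tight as 0.5 SD, that would happen about half the time even if the two durations were truly equal.

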### Sample size calculation

We aim to assess non-inferiority of 6 weeks distraction compared to 8 weeks measured by PROMIS UE scores. We performed a sample size calculation based on the minimal clinically important difference (MCID) of the PROMIS UE questionnaire. The MCID is the smallest difference that patients perceive as beneficial. Previous studies report a MCID of 9.0 points for PROMIS UE with a standard deviation of 11 [32]. Non-inferiority will be considered if the mean difference with 95% confidence interval (95% CI) is no more than 9.0 points lower in the 6-week group compared to the 8-week group. To detect non-inferiority with 90% power, and a one-sided confidence level set at 97.5%, and 5% estimated loss to follow-up, we aim to include 68 patients. Each month, it is estimated that 4 patients will be eligible and willing to participate, resulting in an inclusion time of 2 years.

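### Pain, MHQ and five other secondary outcomes are hypothesised to show no difference but are tested for superiority, which can reject that hypothesis but cannot support it

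*Protocol article*

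**What the plan says.** The abstract's Background paragraph asks whether distraction can safely be shortened from 8 to 6 weeks while "maintaining the improvement in physical function and pain".

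Study objectives sets two hypotheses of no difference at 1 year:
- "We hypothesize that there is no difference between groups in terms of pain intensity, patient satisfaction, joint stiffness, thumb function"; the sentence goes on to range of motion and strength.
- "We hypothesize that there is no difference in hand health status measured with the Michigan Hand Outcome Questionnaire (MHQ").

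The same section words other outcomes as open questions. For complications and conversion to surgery: "We will investigate if there is a difference in adverse event rate and treatment failure at 1 year". For minimal joint space width, the plan is to "test if there is a difference between the two groups".

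The Statistical analysis section applies one approach to all secondary hypotheses: "Regarding the secondary hypotheses, we will test for superiority between the 6-week and 8-week group". It repeats this for MHQ, the four VAS scores, range of motion and strength, and gives P < 0.05 as the significance threshold. The same hypotheses and tests are carried forward to 2 and 5 years.

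A margin and a confidence-interval rule exist only for the primary outcome, the PROMIS upper-extremity score (PROMIS UE). Under Sample size calculation, non-inferiority holds if the difference with its 95% CI "is no more than 9.0 points lower in the 6-week group compared to the 8-week group".

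**The concern.** For seven outcomes (pain, satisfaction, stiffness, thumb function, range of motion, strength and MHQ), the hypothesis and the test point in opposite directions. The expected result is no difference, but the test can deliver only a finding of difference or a failure to find one. Failure to find one is not evidence of similarity, and it becomes more likely as the data become less precise. For function, the protocol avoids this problem by using a margin and a CI. For pain, which the abstract names beside function, it gives neither.

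What is at stake is the secondary conclusion on pain and hand health. If 6 weeks truly gave less pain relief, a non-significant P value would agree with the stated hypothesis and could be taken as support for shortening the treatment. The plan gives no other way to judge these hypotheses.

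**Working it through.** **1. The plan's own figure.** Inputs from Sample size calculation: margin 9.0, SD 11, one-sided 97.5% confidence (z = 1.960), 90% power (z = 1.282), 5% loss. A true difference of 0 is assumed.

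n per arm = 2 × 11² × (1.960 + 1.282)² / 9² = 31.4, rounded up to 32. Total 64; 64 / 0.95 = 67.4, rounded up to 68. This matches the stated 68, so about 32 evaluable patients per arm is the right basis for what follows.

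**2. Precision for a secondary outcome.** With 32 per arm, the standard error of a difference in means is SD × √(2/32) = 0.25 SD. With t(0.975, 62 df) = 2.00, the 95% CI half-width is 2.00 × 0.25 SD = 0.50 SD.

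**3. Chance of a non-significant result when 6 weeks is truly worse.** Two-sample t test, 62 df, two-sided 0.05 (the protocol does not state the sidedness of these tests, so two-sided is assumed). Noncentrality = deficit / (0.25 SD); the miss probability is 1 minus the power.

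| True deficit | Noncentrality | Missed |
|---|---|---|
| 0.3 SD | 1.2 | 78% |
| 0.4 SD | 1.6 | 65% |
| 0.5 SD | 2.0 | 50% |
| 0.6 SD | 2.4 | 34% |
| 0.7 SD | 2.8 | 21% |

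**4. On the 0 to 100 VAS for pain.** The protocol gives no SD for VAS pain, so 20 to 30 is assumed.

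| Assumed SD | CI half-width | 10-point deficit missed | 15-point deficit missed |
|---|---|---|---|
| 20 | 10.0 | 50% | 16% |
| 25 | 12.5 | 65% | 34% |
| 30 | 15.0 | 74% | 50% |

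**5. On the MHQ (0 to 100).** The SD is again assumed. A 10-point deficit is missed 25%, 41% or 50% of the time for an SD of 15, 18 or 20.

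**6. What a pain margin would demand.** The protocol gives no margin for pain, so 10 to 20 points is assumed. With 32 per arm, SD 25, no true difference and one-sided 0.025 (normal approximation), the power to show non-inferiority is 36%, 67% and 89% for margins of 10, 15 and 20 points. Across SD 20 to 30 and these margins it runs from 27% to 98%.

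**The case against.** The strongest reply is that the protocol never says how a non-significant secondary result will be interpreted. The Methods paragraph of the abstract describes the secondary outcomes as serving to identify differences between groups, and a difference test fits that purpose. On this reading, the no-difference sentences are loosely worded null hypotheses. Pain is formally secondary: the primary objective names only PROMIS UE, and a margin on the primary outcome with difference tests on the rest is a common design.

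Much of this stands, and it rules out three stronger readings:
- A reader might infer that the plan will count P ≥ 0.05 as proof that pain relief is maintained. No section says so; this is a risk of misreading, not a stated rule.
- A reader might extend the point to every secondary outcome. Joint space width, adverse events and treatment failure are posed as open questions, so a difference test suits them.
- A reader might conclude that a relevant loss of pain relief would usually be missed. The figures do not support that in general: a 15-point VAS deficit is missed 34% of the time at SD 25, and a 10-point MHQ deficit 41% at SD 18. The protocol does not define a relevant difference on either scale.

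The reply does not remove the mismatch. Study objectives still hypothesises no difference, Statistical analysis still assigns those hypotheses a test that cannot support them, and the abstract still puts maintained pain improvement in the aim. This is stated text, not detail left to an analysis plan, and an analysis plan faithful to it would carry the mismatch forward.

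**Conclusion.** The point holds for the seven outcomes with a no-difference hypothesis, as an inconsistency between hypothesis and test that creates a risk of misinterpretation. With 32 per arm, a non-significant result is compatible with deficits of around half an SD or more, so it cannot show that pain relief is maintained.

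The half-SD figures rest on 32 evaluable patients per arm and a two-sided 0.05 test. The VAS and MHQ figures also rest on assumed SDs. The SD that matters is that of the quantity finally compared, whether 1-year score or change from baseline.

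A compulsory non-inferiority margin for pain and MHQ does not follow from the documents. They give no margin or SD for either scale, and the trial was sized for PROMIS UE alone. The primary analysis and the total of 68 are not in question. The change is worth making because it costs little and affects what the trial may conclude about pain.

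**What to change.** **Study objectives:** replace the no-difference hypotheses for pain, satisfaction, stiffness, thumb function, range of motion, strength and MHQ with estimation of the 6-week minus 8-week difference at 1 year. Leave joint space width, adverse events and treatment failure as they are.

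**Statistical analysis:** for each of the seven outcomes, report that difference with its 95% CI. State that P ≥ 0.05 will not be reported as no difference or as a maintained benefit. Base any statement that pain relief is maintained on the VAS pain CI, judged against a margin if the sponsor can justify one before the 1-year data are analysed. If no margin can be justified, report the CI and make no claim of maintenance. Use the same wording at 2 and 5 years.

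**Cost:** a few sentences, with no extra patients or data. The downside is that, with 68 patients, the pain result may be inconclusive, and the report would have to say so.

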## Background

One out of three people aged 55 years and older has radiographic signs of carpometacarpal osteoarthritis of the thumb joint (CMC1 OA) [1–3]. The prevalence increases with ageing to 90% for adults aged 80 years and older [1–3]. Patients with symptoms of CMC1 OA are initially offered non-operative treatment including splints, analgesics, and hand therapy to reduce pain [4]. If these interventions do not offer sufficient relief, surgical treatment can be considered [4–6]. There are numerous variations in surgical treatment for CMC1 OA. There is, however, no evidence for the superiority of individual techniques regarding pain and functional outcome [5–7]. Trapeziectomy alone, or combined with ligament reconstruction and tendon interposition or suspension arthroplasty, carries the long-term risk of metacarpal subsidence with or without persisting symptoms [5–9]. Prostheses are associated with loosening, subluxation, fracture, and synovitis, potentially requiring revision surgery [5–10]. Arthrodesis of the CMC1 joint reduces range of motion and has the associated risk of non-union resulting in revision surgery [11]. For patients with persisting symptoms of CMC1 OA requiring surgical intervention at a relatively young age, other techniques that preserve the joint and are less invasive may be more desirable.

Joint distraction is a joint sparing treatment for relatively young patients (< 65 years of age) with symptoms of OA and aims to postpone or prevent an invasive surgical intervention [12–15]. Previous evidence on ankle and knee OA shows that joint distraction can result in sustained clinical improvement with actual repair of joint cartilage after treatment [12, 14–18]. Van der Woude et al. [15] showed persisting pain reduction and greater physical function compared to baseline at 5 year follow-up among patients who underwent knee distraction. Another study demonstrated an almost 50% (8/17) joint survival rate after 9 years [14].

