Joint distraction is also feasible for the osteoarthritic CMC1 joint [19]. Nowadays, to our knowledge, more than 50 patients with persisting symptoms of CMC1 OA despite non-operative therapy were treated with CMC1 joint distraction. Recent follow-up results of 20 patients who underwent CMC1 joint distraction shows that in 19 of 20 patients an invasive surgical intervention was postponed for at least 2 years (unpublished data). On average, all patients experienced less pain and better physical function after 2 years. Unpublished data of the first 5 patients shows that all patients were still satisfied 5 years post-distraction without further surgical interventions.

Distraction of the CMC1 joint is currently applied for 8 weeks. However, the duration of knee joint distraction has been decreased from 8 to 6 weeks [17]. This is based on results of 2 previous studies that report similar clinical results at 1 year and less pin tract infections among patients in the 6-week group [17, 18]. Pin tract infections occurred in 85% of patients in the 8-week group versus 55% in the 6-week group [17]. During CMC1 joint distraction, pin-tract infections occur in approximately 1 of 3 patients and are usually adequately treated with oral antibiotics (unpublished data of 40 patients). It is unknown if shortening of the CMC1 joint distraction duration from 8 to 6 weeks will also result in less adverse events and still achieve sufficient clinical benefits for patients. Therefore, we designed this study protocol for a randomized controlled non-inferiority trial to compare 6 weeks with 8 weeks of CMC1 joint distraction.

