#### Secondary study parameters

Patient characteristics: gender, age at operation, work status, marital status, and level of highest education.Michigan Hand Outcome Questionnaire (MHQ - Dutch Language Version): a validated 57-item questionnaire that gauges hand health status on a scale from 0 to 100 with higher scores indicating better hand health status [26].Patient Health Questionnaire (PHQ-2): 2-item questionnaire with scores from 0 representing ‘lowest level of depression’ to 6 ‘highest level of depression’ [27].Pain Catastrophizing Scale (PCS-4): 4-item questionnaire rated on a 5-point Likert scale with scores ranging from 0 indicating ‘no catastrophic thinking’ to 16 ‘worst possible catastrophic thinking’ [28].Visual analogue scale (VAS) scores for pain, patient satisfaction, thumb stiffness and function: with scores from 0 representing ‘no pain at all’ or ‘fully satisfied’ or ‘no stiffness at all’ or ‘optimal function’ to 100 ‘worst pain possible’ or ‘not at all satisfied’ or ‘worst stiffness possible’ or ‘worst possible function’.Range of motion obtained by an independent certified hand therapist:Thumb opposition by Kapandji scores (range 0–10)Palmar thumb abduction (degrees) by Pollexograph [29]Strength measures* (in kg) obtained by an independent certified hand therapist:Grip strength measured with a Jamar hand dynamometerKey and tip pinch strength measured with baseline pinch gauge**Strength measures are recorded as the average of three attempts*Radiographs will be obtained in three different views (posteroanterior, lateral and Bett’s view). Joint space (in mm) will be scored by an independent blinded radiologist.Adverse events: classified according to the Clavien-Dindo classification of surgical complications ranging from grade I (minor complication) to grade V (death) [30]. Any adverse event that occurs during the distraction period or at follow-up will be administered and classified. For example, pin tract infections that are adequately treated with oral antibiotics will be classified as grade I (minor complication). In the unlikely event that intravenous antibiotics and a hospital admission is needed, this will be rated as a grade II complication.Treatment failure: defined as conversion to an invasive surgical procedure (f.e. trapeziectomy) after distraction therapy due to ongoing symptoms of CMC1 OA.

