#### Postoperative appointments and measurements

The study phases and data collection time points are shown in Fig. 3. The Standard Protocol Items: Recommendations for Interventional Trials (SPIRIT) checklist is provided as Additional file 1. In case of any problems or concerns regarding the distraction device, extra visits will be scheduled if needed.

After placement of the distractor device, a thermoplastic splint is applied and hygiene instructions are given. Patients can go home on the same day of surgery. It is not allowed to drive a car, lift objects or bear weight with the operated hand during the duration of distraction therapy. Three weeks (for group A) or 4 weeks (for group B) after placement of the distractor device, patients are seen at the outpatient clinic. Only VAS pain scores will be collected at this time point and no other questionnaires or measurements are assessed. Any adverse events will be registered if needed.

The distractor device will be removed at the outpatient clinic after 6 weeks for patients in group A and after 8 weeks for patients in group B. After removal, a radiograph is obtained and hand therapy commences according to a standard protocol for rehabilitation after surgical intervention. Patients are informed not to perform heavy weight bearing exercises of the thumb and index finger up to 12 weeks after removal of the distractor device. There is no other relevant concomitant care permitted or prohibited during the trial. A short overview of the exercises and timeline is provided in Additional file 2.

At 3 months, 6 months, and 1 year after placement of the distractor device (regardless of group), patients will be seen for follow-up measures at the outpatient clinic. At these visits, several questionnaires will be completed, radiographs of the thumb will be obtained, and any adverse events that may have occurred will be evaluated and registered. The same measurements are collected at 2 years and 5 years after initial surgery to evaluate the long-term effects of joint distraction. If patients underwent other surgical interventions for ongoing symptoms of CMC1 OA, despite joint distraction of the affected hand, this will be registered as treatment failure.

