We will perform the same statistical tests and analysis as mentioned above at 2 years and 5 years post-distraction to study the long-term results. Incomplete data will be adequately described. We will use multiple imputation for any missing data or means for missing values.

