### Withdrawal

Participants can leave the study at any time for any reason if they wish to do so, without any consequences. If a patient wishes to withdraw during the distractor period, the distractor can be removed in the outpatient clinic and standard treatment will continue. After removal of the distractor, a patient is also free to discontinue participation by refusing to complete questionnaires or follow-up imaging. We do not anticipate any circumstance in which the investigator would recommend the patient withdraws from the study since the potential risks and complications expected are limited and not life-threatening or harmful (see the section “Potential benefits and risks assessment”).

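### Conversion to surgery is compared only as a fixed-time proportion; at 2 and 5 years a time-to-event analysis would be a cheap, minor improvement

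*Protocol article*

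**What the plan says.** All references are to the protocol article.

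- **Definition.** Secondary study parameters gives treatment failure as "defined as conversion to an invasive surgical procedure (f.e. trapeziectomy) after distraction therapy due to ongoing symptoms of CMC1 OA". It is an event that happens on a date.
- **Analysis.** Statistical analysis states "We will analyse the difference between groups in the proportion of participants who are classed as treatment failure at 1 year", and then "We will perform the same statistical tests and analysis as mentioned above at 2 years and 5 years post-distraction". Failure is therefore compared as a proportion at three fixed times. No time-to-event analysis is stated.
- **Missing data.** The same section says "We will use multiple imputation for any missing data or means for missing values". The rule is general and makes no exception for a yes/no outcome.
- **Follow-up.** Postoperative appointments and measurements schedules visits at 3 months, 6 months and 1 year, and then "The same measurements are collected at 2 years and 5 years after initial surgery". No visit is listed between years 2 and 5.
- **Loss.** Under Withdrawal, after removal of the distractor "a patient is also free to discontinue participation by refusing to complete questionnaires or follow-up imaging". The only loss figure is 5%, in the sample size paragraph for the 1-year primary outcome.
- **Purpose.** Background says that joint distraction "aims to postpone or prevent an invasive surgical intervention". It also reports that surgery was postponed for at least 2 years in 19 of 20 earlier thumb patients.

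**The concern.** Part of the treatment's purpose is delay of surgery, and follow-up runs to 5 years with withdrawal permitted. A proportion at a fixed time needs a yes/no status for everyone at that time. A patient last seen unconverted at year 2 has no 5-year status, so must be left out, counted as a non-failure or imputed. The stated rule allows imputation by a mean, which makes no use of the two years that were observed.

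At stake is the long-term failure risk per arm, a figure that patients and surgeons are likely to quote. If loss is appreciable, that figure moves with the handling rule, and the article leaves the choice between two rules open. The timing of conversions within an interval is also not used.

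**Working it through.** **The plan's own figure.** The only sample size is for PROMIS UE: margin 9.0, SD 11, 90% power, one-sided 2.5%. Per arm n = 2 × (1.960 + 1.282)² × 11² / 9² = 31.4, so 32; total 64; 64 / 0.95 = 67.4, so 68. This reproduces the stated 68. The point here does not depend on it. No event count or power is given for treatment failure.

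**What filling with a mean does.** Let an arm have K patients with known status, F of them failures, and m with unknown status. Giving each unknown patient the arm's mean F/K yields (F + m·F/K) / (K + m) = F/K. That is the completer proportion exactly, so the completer result below applies to one of the two rules that the plan names.

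**Model (assumptions).** Failure and loss have constant hazards, loss is independent of failure, and a conversion seen before loss stays known. With true 5-year failure p and 5-year loss L:

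- h = −ln(1 − p), c = −ln(1 − L)
- seen unconverted at 5 years: s = (1 − p)(1 − L)
- observed failures: A = h/(h + c) × (1 − s)
- lost counted as non-failures: A
- completers (or arm mean filled in): A/(A + s)

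**Example, p = 20%, L = 40%.** h = 0.2231, c = 0.5108, s = 0.80 × 0.60 = 0.48. A = 0.2231/0.7339 × 0.52 = 15.8%. Completers: 0.158/(0.158 + 0.48) = 24.8%.

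**Range:**

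| True 5-year failure | 5-year loss | Completers or arm mean | Lost as non-failures |
|---|---|---|---|
| 12% | 5% | 12.3% | 11.7% |
| 12% | 25% | 13.7% | 10.5% |
| 20% | 5% | 20.4% | 19.5% |
| 20% | 20% | 22.0% | 18.0% |
| 20% | 40% | 24.8% | 15.8% |
| 35% | 25% | 38.7% | 30.7% |
| 40% | 40% | 47.1% | 32.0% |

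The 12% row extends the article's 1 of 20 by 2 years at a constant hazard: 1 − 0.95^2.5 = 12.0%. Every other failure rate, and every 5-year loss rate, is an assumption.

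**Simulation** (3000 runs, 34 per arm, same model). With true 20% failure and 5%, 20% and 40% loss:

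- completers: 20.5%, 21.7%, 24.6%
- lost as non-failures: 19.6%, 17.8%, 15.8%
- Kaplan-Meier: 20.0%, 19.8%, 19.9%

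For 40% versus 15% with 40% loss, a true difference of 25 points is estimated as 28.2 (completers), 20.2 (lost as non-failures) and 25.0 (Kaplan-Meier).

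**Power** (completers, lost as non-failures, log-rank): 18%, 19%, 18% for 20% versus 10% at 20% loss; 53%, 55%, 55% for 40% versus 15% at 40% loss. There is no material gain.

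**The case against.** The strongest reply is that nothing here is an error. A between-arm difference in failure at a fixed time is an interpretable estimand for a secondary outcome, and it speaks directly to preventing surgery. That stands.

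Several stronger readings are tempting, and the article does not support them:

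- **That the plan ignores delay.** With analyses at 1, 2 and 5 years, a conversion in month 3 counts three times and one in month 59 only at the last. Coarse timing is kept. The earlier 19 of 20 result is itself a fixed-time proportion.
- **That the planned handling is biased throughout.** Multiple imputation is named first. If it uses last known status, it rests on an assumption comparable to independent censoring, and no bias was shown for it. The calculation covers the means option and the two simple alternatives. Counting lost patients as non-failures is not something that the article proposes.
- **That the trial loses power.** It does not, as the figures above show.
- **That a large distortion is to be expected.** At failure extrapolated from 1 of 20 by 2 years, the shift is about 0.3 points at 5% loss and under 2 points at 25% loss. One patient in an arm of 34 is 1/34 = 2.9 points.

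Two cautions apply to the remedy as well. If dissatisfied patients leave and have surgery elsewhere, Kaplan-Meier is biased too. The article says that conversions are registered but not that their dates are.

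What survives the reply is narrower. The article itself fixes the method and allows means for any missing value, and the long-term estimate then depends on which rule is used.

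**Conclusion.** The point holds as a cheap improvement of minor severity. At 1 year the planned proportion is adequate. At 2 and 5 years, comparing proportions discards timing between visits. If means are used for patients lost early, each arm's failure risk becomes the completer proportion and is biased upward; counting them as non-failures would bias it downward. The shift is under 1 point at 5% loss with failure of 20% or less, about 2 to 5 points at 20% to 40% loss with 20% failure, and up to about 8 points in the most extreme case tried (40% failure, 40% loss).

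These sizes rest on constant hazards, loss unrelated to the risk of surgery, and conversions remaining known; the 5-year rates are assumed. The gain is a less biased long-term estimate and a description of delay.

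**What to change.** In Statistical analysis:

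1. Keep the between-arm risk difference for treatment failure at 1 year.
2. For the 2- and 5-year analyses, define time from placement of the distractor to conversion, censored at last contact. Show Kaplan-Meier curves by arm, compare arms by log-rank test or Cox model, and report Kaplan-Meier risk differences with 95% CI at 1, 2 and 5 years.
3. Exempt treatment failure from mean imputation.
4. State the assumption that loss is unrelated to the risk of surgery, and report the number lost and when, by arm.

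Cost: a change of wording, plus recording the date of each conversion and of each patient's last contact. The sample size stays at 68 and no visit is added.
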